## Methods and Analysis

### Design

This is a multi-center, prospective, controlled study (**Figure 1**). The study has been approved by the Ethics Committee of the IRCCS Regina Elena National Cancer Institute and by the Ethics Committee of the Sapienza University of Rome.

**Figure 1 f1:**
[figure not shown]
Flow chart of the study protocol.

Specific aims of our study are

**Primary outcomes:**

To evaluate serum/plasma concentrations of complement (C3, C4, C4a, and C9), Fibrinogen, Factor VIII (FVIII), Factor X (FX), D-dimer (DD), PC, PS in relapsing-remitting MS (RRMS) patients and healthy people.

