## Abstract

**Introduction:**

Multiple sclerosis (MS) is a demyelinating disease of the central nervous system with an underlying immune-mediated and inflammatory pathogenesis. Innate immunity, in addition to the adaptive immune system, plays a relevant role in MS pathogenesis. It represents the immediate non-specific defense against infections through the intrinsic effector mechanism “immunothrombosis” linking inflammation and coagulation. Moreover, decreased cerebral blood volume (CBV), cerebral blood flow (CBF), and prolonged mean transit time (MTT) have been widely demonstrated by MRI in MS patients. We hypothesized that coagulation/complement and platelet activation during MS relapse, likely during viral infections, could be related to CBF decrease. Our specific aims are to evaluate whether there are differences in serum/plasma levels of coagulation/complement factors between relapsing-remitting (RR) MS patients (RRMS) in relapse and those in remission and healthy controls as well as to assess whether brain hemodynamic changes detected by MRI occur in relapse compared with remission. This will allow us to correlate coagulation status with perfusion and demographic/clinical features in MS patients.

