**Figure 3 f3:**
[figure not shown]
Workflow of circulating miRNA profiling. For circulating miRNA profiling blood samples from patients will be processed. In particular, circulating RNA will be extracted from serum samples with a column-based extraction method. Total and small RNA quality will be assessed by Bioanalyzer. Then, total RNA will be labelled for the hybridization to Human miRNA Microarray Release 21 (Agilent) containing probes for 2549 human miRNAs. Microarray data will be subjected to bioinformatic analysis to identify a signature of miRNAs differentially expressed. Deregulated miRNAs pathway analysis and correlations analysis with clinical variables will be performed.

Total RNA will be labeled and hybridized to Human miRNA Microarray Release 21 (Agilent) containing probes for 2549 human microRNAs from the Sanger database. Each slide is an 8 x 15K format (~15,000 features printed in an 8-plex format, eight individual microarrays on a 1” x 3” glass slide) printed using Agilent’s 60-mer Inkjet Technology, which, unlike competitive platforms, synthesizes 40–60-mer oligonucleotide probes directly on the array, resulting in high-purity, high fidelity probes. This miRNA platform requires small input amounts of total RNA—in the 100 nanogram range—because it uses a high-yield labeling method and does not require size fractionation or amplification steps that may introduce undesired bias during miRNA profiling.

Scanning and image analysis will be performed using the Agilent DNA Microarray Scanner (P/N G2565BA) equipped with extended dynamic range (XDR) software according to the Agilent miRNA Microarray System with miRNA Complete Labeling and Hyb Kit Protocol manual. Feature Extraction Software (Version 10.5) will be used for data extraction from raw microarray image files using the miRNA_105_Dec08 FE protocol. microRNA Microarray data will be subjected to stringent quality controls and then analyzed by the Bioinformatic Unit.

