### Data Analysis

#### Sample Size Calculation

Overall 90 subjects (30 for each group) will be enrolled to compare the level of complement C4a (55). By using the ANOVA test, this sample size will allow detection of effect size values [delta=(miA–miB)/sigma] equal to at least 0.71, with a statistical power of 80%, to a level of significance of 5%.

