#### Statistical Methods

Descriptive statistics will be used to summarize pertinent study information. Correlations between quantitative variables will be assessed with the Pearson r correlation. The associations will be analyzed by the Fisher exact test or Chi Square test for trends. Comparisons between disease subgroups and control group will be carried out for different variables, using either Student’s *t-*test or analysis of variance (ANOVA). If the ANOVA shows a statistical difference between subgroups, a post-hoc analysis with Bonferroni correction for multiple comparisons will be performed. For non-normally distributed data, non-parametric (Mann Whitney-U or Kruskal-Wallis-H) tests will be used. The level of significance is set at p ≤ 0.05 (SPSS version 20.0, SPSS Inc., Chicago, Illinois, USA).

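### Ten co-equal primary markers are each tested at 5% with no correction across markers, although only C4a was sized: the chance of at least one false primary finding is up to 40%

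*Protocol article*

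**What the plan says.** - **Primary outcomes** (under Design): ten markers, unranked, in patients and healthy people: "complement (C3, C4, C4a, and C9), Fibrinogen, Factor VIII (FVIII), Factor X (FX), D-dimer (DD), PC, PS".
- **Sample Size Calculation**: "Overall 90 subjects (30 for each group) will be enrolled to compare the level of complement C4a". With ANOVA, 80% power and a 5% significance level, the detectable standardised difference is given as 0.71. No other marker is sized.
- **Statistical Methods**: "Comparisons between disease subgroups and control group will be carried out for different variables", by t-test or ANOVA, with Mann-Whitney or Kruskal-Wallis for non-normal data. "The level of significance is set at p ≤ 0.05".
- **The only multiplicity rule**, in the same section: "If the ANOVA shows a statistical difference between subgroups, a post-hoc analysis with Bonferroni correction for multiple comparisons will be performed".

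The article states no order among the ten markers, no split of the 5% level, and no rule for how many markers must be significant.

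**The concern.** A primary outcome carries the study's main conclusion, and the 5% level is meant to bound the chance that this conclusion is false. Here ten outcomes hold that position and each has its own 5%. The Bonferroni step does not help, because it works on the pairs among relapse, remission and control after one marker's ANOVA is significant. It says nothing about the other nine ANOVAs.

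The sections also do not match. One section has ten primary outcomes, and another is sized as if there were one. The stated 80% power at a 5% level describes a study of C4a alone. A reader who later sees one or two of ten markers significant could not tell how surprising that is, because the plan does not fix the error rate for the set.

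This is more than detail left to an unseen analysis plan. The article addresses multiplicity and states a rule, and that rule leaves the primary set uncontrolled. Which outcomes are primary is itself a protocol decision.

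**Working it through.** **Inputs from the article:** 10 primary markers; 3 groups of 30; significance level 0.05; detectable difference 0.71 with 80% power for C4a. **Assumed, because the article does not give it:** the correlation between markers.

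**1. Reproduce the plan's own figure.** One-way ANOVA with 3 groups of 30 has 2 and 87 degrees of freedom. If one group differs from two equal groups by d standard deviations, the noncentrality is 30 × (2/3) × d². At d = 0.71 this is 30 × 0.6667 × 0.5041 = 10.08. The critical F at 0.05 is 3.10 and the power is 80.4%. The difference detectable with 80% power is 0.706. The stated 0.71 is therefore reproduced, for one marker at the full 5%.

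**2. Error across ten independent markers, all nulls true.** 1 − (1 − 0.05)^10 = 1 − 0.599 = 0.401, or 40%.

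**3. Error with correlated markers.** Trials of 3 × 30 subjects and ten null markers were simulated (20,000 per setting; four settings repeated with 100,000), counting trials with at least one ANOVA below 0.05:

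| Assumed equal correlation | Chance of at least one false finding |
|---|---|
| 0 | 40% |
| 0.3 | about 36% |
| 0.5 | 29 to 30% |
| 0.7 | 22% |
| 0.8 | 18% |

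With correlation of 0.3 to 0.7 inside a pathway (complement; procoagulant; protein C and S) and 0.1 elsewhere, the figure is 38% down to 31%.

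**4. Does the planned post-hoc step repair this?** Suppose a finding also needs a Bonferroni-significant pair. The figure is then 35% at correlation 0 and 25% at 0.5. It falls a little but stays far above 5%.

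**5. What control across all ten would cost.** Plain Bonferroni gives 0.05/10 = 0.005 per marker, and 1 − 0.995^10 = 4.9% overall if the markers are independent. The critical F rises to 5.63. With 30 per group, power at 0.71 falls from 80.4% to 49.4%, and the detectable difference rises from 0.71 to 0.91 (one group different). Keeping 80% power at 0.71 would need 49 per group.

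**The case against.** - **The markers are not independent.** This stands. Four are complement components, and the Introduction describes protein S as a cofactor of activated protein C. So 40% is an upper figure for the ANOVA route, not an estimate. Even at a correlation of 0.8 the figure is 18%, more than three times the nominal level.
- **This is non-randomised biomarker research, and no rule says that one significant marker makes the study positive.** Also true; that such a result would be reported as positive is an inference. But the article calls these outcomes primary and says that it aims to validate a pathogenetic role, so the error rate for the set matters.

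Three stronger readings are tempting, and the documents do not support them:

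- **The microarray yields about 127 false hits.** A reader might multiply 2549 by 0.05. The array section describes a separate bioinformatic analysis with no stated threshold, and nothing there says that each microRNA is tested at 0.05. The array is also a key secondary outcome and adds nothing to the primary error.
- **Relapse versus remission should be the sole primary contrast.** The Abstract's aim is a comparison "between relapsing-remitting (RR) MS patients (RRMS) in relapse and those in remission and healthy controls", which is three groups, and the sizing uses ANOVA. Replacing that with one pair is a preference, and it would lower power at 0.71 to about 77%.
- **The error exceeds 40% because t-tests are allowed.** Three unadjusted t-tests per marker would give 73% at correlation 0 and 57% at 0.5. The article does not say that the three-group primary comparison will be made this way, and it sizes that comparison on ANOVA.

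**Conclusion.** The point holds for the ten primary markers. As written, the plan has ten co-equal primary outcomes, one of them sized, and no control of error across them. The chance of at least one false primary finding is up to 40%, and about 22 to 36% for equal correlations between 0.7 and 0.3. These figures assume that all ten nulls are true and that each marker is tested once by ANOVA at 0.05; the correlations are assumptions. The defect does not touch the C4a calculation, which is correct for a single primary outcome when one group differs from the other two. It should be settled before the data are analysed.

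**What to change.** **Preferred.** In Primary outcomes and Statistical Methods, name C4a as the single primary outcome, tested by the three-group ANOVA at 5% with the planned Bonferroni post-hoc pairs. Move the other nine markers to key secondary, with Holm correction across the nine marker-level tests.

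**Alternative.** Keep all ten as primary, apply Holm across the ten marker-level tests, and restate the detectable effect. Plain Bonferroni at 0.005 is the conservative reference: 0.91 instead of 0.71, and 49% power at 0.71.

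**Cost.** The preferred change is mainly wording and needs no more subjects. It keeps the stated 80% power at 0.71 for C4a. The downside is that the other nine markers face a stricter threshold: the smallest of their p-values must be at most 0.05/9 = 0.0056. Because the list of primary outcomes changes, the registration entry must be checked and brought into line.

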**Key secondary outcomes:**

To evaluate serum/plasma concentrations of Prothrombin Time (PT), Activated Partial Thromboplastin Time (aPTT), Factor II (FII), antithrombin III (ATIII), von Willebrand factor (vWF), soluble (s)TM and soluble (s)EPCR, Angiopoietin-1, Angiopoietin-2, FIII or TF, TM, Tie-2, Vascular Endothelial Growth Factor (VEGF), APLs, lupus anticoagulant (LA), complete blood count (CBC), viral serological assays, and microRNA microarray in relapsing-remitting MS (RRMS) patients and healthy people.

**Additional secondary outcomes:**

To assess relative CBF, CBV, and MTT by DSC 3.0-T MRI in relapsing MS patients compared to remitting MS patients.To evaluate number and volume of enhancing lesions in relapsing MS patients compared to remitting MS patients.To evaluate the relationships between laboratory data, demographic/clinical (age, gender, disability and disease duration) features, and MRI perfusion findings in the patients’ groups.

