#### MRI Procedures

All RRMS patients will undergo the 3.0-T MRI within two weeks of enrollment. We will use DSC perfusion technique acquired during the first pass of gadolinium to estimate perfusion features inside the damaged tissue of relapsing and remitting MS patients.

DSC MR images will be acquired on the axial plane during the first pass of a standard-dose bolus (0.1 mmol/kg) of gadopentetate dimeglumine (Magnevist; Berlex Laboratories, Wayne, NJ, USA) with a gradient-echo T2-weighted echo-planar imaging sequence. A contrast will be injected at a rate of 3,5 mL/sec, followed by a 20-mL bolus of saline also at a rate of 3,5 mL/sec. A total of 60 images will be acquired at 1-sec intervals, with the injection occurring at the fifth image, for a total acquisition time of 2 min 16 s. The imaging parameters will be as follows: TR/TE = 2140/30 ms, flip angle = 30°, slice thickness = 4 mm, FOV = 280 mm, matrix = 128x128.

The following hemodynamic parameters will be obtained from the concentration–time curves: the relative CBV (rCBV, i.e., the fraction of the tissue volume occupied by blood), the relative CBF (rCBF, i.e., the volume of blood in a given amount of tissue per unit of time), and MTT (the average time it takes for the contrast agent to travel through the tissue vasculature, for the ideal case of an instantaneous bolus injection) by using NordicIce software package.

Thus, we will use the leakage correction function provided by NordicIce software to minimize this effect both on Gadolinium and on non-Gadolinium enhancing lesions, in which a subtle leakage of contrast agent cannot be excluded.

Finally, rCBF, rCBV, and MTT values will be extracted from different sites of the brain damaged by MS (hyperintense T2-w lesions, Gadolinium enhancing T1-w lesions, periventricular and frontal NAWM, thalamus, and putamen nuclei and head of the caudate bilaterally). To exclude interobserver and to minimize intra-observer variability, each data set will be reviewed by two expert radiologists at the same time (**Figure 4**).

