## Conclusion

In this study, it will be important to identify the exact links between activation of coagulation/complement system and brain hemodynamic changes with cerebral hypoperfusion.

We hypothesized that cerebral hypoperfusion in all forms of MS could be the result of the blood flow deceleration mostly in the venous vessel bed during brain inflammatory-thrombotic processes in the course of relapses. Systemic immune activation during the infections influences innate brain immunity and, consequently, adaptive immune response (79, 80). When recurrent and chronic infections, which manifest systemically with immunothrombosis (13), directly or indirectly involve the CNS, it could lead to acute and chronic neuroinflammation. Constant crosstalks between immune cells and coagulation are seminal for an effective immune response (12). While many efforts have been carried out to better define the function of innate immune cells in order to modulate their potential pathogenetic role in MS with specific therapeutic action (5, 6), the coagulant component of innate immunity, which is well studied in animals, has not been sufficiently evaluated in humans. Our working hypothesis is that relapsing patients could have a pro-coagulant condition that may be correlated with blood flow deceleration and the presence of serological indicators of ongoing infection. Whether or not we found correlations between laboratory and MRI parameters, we may see the difference between the relapsing and the remitting MS patient groups. One could argue that peripheral laboratory parameters measured in this study may not fully reflect nor be specific for pathophysiological events occurring in the CNS. However, we hypothesize and believe that events at the CNS level, particularly in MS, could partially represent or be a result of systemic diseases such as infections.

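### The coagulation/complement–perfusion link is open to up to 210 unadjusted Pearson tests from the primary markers alone, with no key test named and no multiplicity rule that reaches them

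*Protocol article*

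**What the plan says.** Under Additional secondary outcomes the article plans two kinds of perfusion analysis. One is a group comparison: "To assess relative CBF, CBV, and MTT by DSC 3.0-T MRI in relapsing MS patients compared to remitting MS patients". The other is a relationship analysis: "To evaluate the relationships between laboratory data, demographic/clinical (age, gender, disability and disease duration) features, and MRI perfusion findings in the patients’ groups".

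The laboratory side is wide. The primary outcomes are "complement (C3, C4, C4a, and C9), Fibrinogen, Factor VIII (FVIII), Factor X (FX), D-dimer (DD), PC, PS", which is ten markers. The key secondary outcomes begin with "Prothrombin Time (PT), Activated Partial Thromboplastin Time (aPTT), Factor II (FII), antithrombin III (ATIII), von Willebrand factor (vWF" and continue through endothelial and angiogenic markers, antiphospholipid antibodies, blood count, virology and a microRNA array.

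The imaging side is wide too. MRI Procedures states that "rCBF, rCBV, and MTT values will be extracted from different sites of the brain damaged by MS", and lists these as "hyperintense T2-w lesions, Gadolinium enhancing T1-w lesions, periventricular and frontal NAWM, thalamus, and putamen nuclei and head of the caudate bilaterally".

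Statistical Methods says "Correlations between quantitative variables will be assessed with the Pearson r correlation" and sets significance at p ≤ 0.05. Its only multiplicity provision is a Bonferroni correction of post-hoc comparisons once an ANOVA is significant.

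The Conclusion opens by saying that "it will be important to identify the exact links between activation of coagulation/complement system and brain hemodynamic changes with cerebral hypoperfusion". The last sentence of the Introduction gives the study's aim as validating a role of coagulation together with brain hemodynamic abnormalities. Neither the outcome list nor the analysis section calls the correlations exploratory.

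**The concern.** The link between coagulation/complement activation and perfusion is the article's mechanistic message. As planned, it can be drawn from any pairing of marker, parameter and site that crosses an unadjusted 5% threshold.

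The Bonferroni rule does not help. It corrects contrasts between groups within one variable after an ANOVA. A correlation has no such contrasts. The MRI comparison has only two groups, because Selection of Subjects excludes controls from contrast MRI. Neither case limits the number of markers, parameters or regions examined.

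At stake is how far a reported link can be trusted. If a null relationship usually yields several nominally significant correlations, a report of one or a few carries little evidence. The same applies to a statement that relapse shows hypoperfusion when it rests on one region and one parameter out of 21.

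**Working it through.** **The plan's own figure.** The only quantitative design figure is in Sample Size Calculation: a standardized difference of 0.71 in C4a, 30 per group, 80% power, 5% level. It reproduces for a three-group ANOVA in which two means are equal and one differs: f = 0.71 × √8 / 6 = 0.335, N = 90, power 80.4%. It is not in dispute, and it says nothing about correlations.

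**Inputs.**
- Primary markers: 10 (Primary outcomes).
- Perfusion parameters: 3, namely rCBF, rCBV and MTT (MRI Procedures).
- Kinds of site: 7, namely T2 lesions, enhancing lesions, periventricular NAWM, frontal NAWM, thalamus, putamen and caudate head, with left and right not counted separately.
- Patients with both blood and MRI: 30 + 30 = 60 (Selection of Subjects).
- Level per test: 0.05, taken as two-sided because the article does not say.

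**Number of tests the plan permits.**
- Perfusion variables: 3 × 7 = 21.
- Marker–perfusion correlations: 10 × 21 = 210.
- With the 13 further quantitative markers as listed under Key secondary outcomes (soluble TM and TM counted separately): 23 × 21 = 483.
- CBF only, ten primary markers: 10 × 7 = 70.
- The six primary coagulation markers only: 6 × 21 = 126.
- NAWM taken as one site: 10 × 3 × 6 = 180.

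**Expected false positives with no true association.** This is the number of tests × 0.05, whatever the dependence: 210 × 0.05 = 10.5. About half, 5.25, would have the hypothesised sign. For 70 tests it is 3.5, for 126 it is 6.3 and for 180 it is 9.0.

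**Threshold.** r = t / √(n − 2 + t²). With n = 60 this gives |r| = 0.254.

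**Chance of at least one false positive among 210.** If the tests were independent, 1 − 0.95^210 = 99.998%. They are not independent, and the article gives no correlations, so a range is needed. Two assumed dependence models were simulated with n = 60, 4,000 replicates and all true marker–perfusion correlations zero.

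Model A uses an equal correlation ρ among the markers and among the perfusion variables:

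| ρ | Chance of ≥ 1 of 210 |
|---|---|
| 0 | 99.98% |
| 0.3 | 99.9% |
| 0.5 | 98.1% |
| 0.8 | 59.7% |

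Model B uses separate correlations among markers, among regions, and between CBF and CBV, with MTT constructed from the other two:

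| Marker / region / CBF–CBV | 210 tests | 483 tests | CBF only, 70 tests |
|---|---|---|---|
| 0.2 / 0.5 / 0.5 | 99.8% | about 100% | 91% |
| 0.3 / 0.7 / 0.7 | 98% | about 100% | 81% |
| 0.5 / 0.8 / 0.8 | 92% | 99% | 66% |
| 0.5 / 0.9 / 0.9 | 83% | 96% | 55% |
| 0.7 / 0.95 / 0.9 | 63% | 77% | 35% |

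**Relapse versus remission, 21 perfusion tests.** Under equal correlation the chance of at least one false positive is 65.9%, 55.5%, 42.8% and 22.8% at ρ = 0, 0.3, 0.5 and 0.8.

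**What a named test would offer.** Detectable r = tanh[(z for α/2 + z for power) / √(n − 3)]. At α = 0.05 and 80% power, tanh[(1.960 + 0.842) / √57] = 0.35. Bonferroni over all 210 tests (0.05/210 = 0.00024) would raise the critical |r| to 0.46 and the detectable |r| to about 0.54.

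**The case against.** The strongest reply is that a journal article condenses the plan, that these correlations stand last in the outcome hierarchy, and that naming a key pair or an adjustment rule is often left to the SAP. That carries weight for severity. It does not remove the point, because the article is not silent: it fixes the method and the threshold, and it confines its only correction to a setting that excludes these tests.

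A second reply is that p ≤ 0.05 is a per-test level and the article never promises family-wise control. That is true, so no promise is broken. The difficulty is claiming an identified link from tests run at that level.

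Several stronger readings are tempting but not supported:
- A reader might infer that at least 210 correlations will be run. The count is what the plan permits. Nothing says every marker is tested at every site, Figure 4 shows NAWM as one mask, and enhancing lesions may be absent in some patients.
- A reader might infer that no perfusion parameter is named anywhere. The Abstract's hypothesis names CBF decrease. Even so, CBF alone leaves 70 tests with the primary markers.
- A reader might infer that the hypothesis cannot fail. The Conclusion states a direction, a pro-coagulant state with slower flow, and allows that correlations may not be found. Wrong-sign results would count against it. For the six primary coagulation markers against CBF, 6 × 7 = 42 tests, only 42 × 0.025 = 1.05 false hits in the supporting direction are expected.
- A reader might infer that a false link is close to certain. That holds for weak to moderate dependence only. All three parameters come from the same concentration–time curves with one global arterial input function, so strong dependence is plausible.
- A reader might infer that therapeutic targets are claimed as findings. The Abstract and the closing paragraph of the Conclusion speak of possibilities and of trials still needed.

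**Conclusion.** The concern holds in this limited form. The link between coagulation/complement markers and perfusion has no key test and no applicable multiplicity control, while the article presents it as something to validate or identify.

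If all 210 primary-marker correlations are run in 60 patients and no association exists, about 10.5 will be nominally significant, roughly half in the hypothesised direction. The chance of at least one is about 60% to over 99%; for the 21 regional group comparisons it is about 23% to 66%. The expected count needs only the number of tests and the 5% level. The probabilities rest on assumed dependence, which the article does not inform, and on complete data in 60 patients.

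This affects an additional secondary outcome and the interpretation built on it. The primary group comparisons are not touched.

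**What to change.** In Additional secondary outcomes and Statistical Methods:

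1. Name one key link test, chosen by the investigators before analysis, at two-sided 5%. Use rCBF, the parameter in the stated hypothesis; one defined region measurable in every patient, such as NAWM; and one marker that represents the hypothesis. C4a, the sample-size marker, is a complement fragment and would not by itself test a pro-coagulant hypothesis, so the choice of marker needs a stated reason.
2. Name one key relapse-versus-remission comparison on the same parameter and region.
3. Label all other correlations and regional comparisons exploratory, and report them with confidence intervals and Benjamini-Hochberg adjusted p-values.
4. In the Abstract's Discussion and in the Conclusion, limit any statement that a link was identified to the named test.

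The cost is wording and a few lines of code, with no new data. The small downside is that unadjusted regional correlations can no longer be presented as established links.
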